#### Interim analyses {21b}

An interim analysis will be performed after recruitment of 15%, 30%, and 60% participants in the trial. It will assess primary outcomes of the study particularly focusing on the safety and efficacy of the infused drug. Safety of the intervention will be monitored in terms of any immediate or serious adverse event that can be observed after the administration of the drug. The efficacy of the intervention will be noted in terms of the patient's improvement in clinical status as compared to the control group.

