### Trial design {8}

This is an adaptive, phase II/III, multi-center, randomized controlled, single-blinded superiority trial with parallel group design to assess the safety and efficacy of single dose of C-IVIG in patients with symptoms of severe COVID-19. Eligible participants will be randomly assigned in 2:1 ratio (206 tests: 103 controls) by block randomization method to receive C-IVIG plus standard of care (intervention group) or only standard of care (control group). The adaptive study design refers to adapting the strategy of trial based on interim analysis at three particular time points [12]. Outcome of the interim analysis will lead to making decision for terminating trial in case of serious adverse events or selecting a higher C-IVIG dose regime in case selected dose of C-IVIG (0.15g/Kg) not found efficacious. A flow chart of the trial design is shown in Fig. 1.

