#### Outcomes {12}

Primary outcome:28-day mortality [time frame: 28 days]All-cause mortality of participants will be monitored for 28 days to assess the safety and efficacy of C-IVIG

Secondary outcomes:Immediate (within 24 h) or serious adverse events (throughout the hospital stay) [time frame: 28 days]Clinical status according to 7 category ordinal Scale [time frame: 28 days (till hospital stay)Not hospitalized and no limitations of activitiesNot hospitalized, with limitation of activities, home oxygen requirement, or bothHospitalized, not requiring supplemental oxygenHospitalized, requiring any supplemental oxygenHospitalized, requiring noninvasive ventilation or use of high-flow oxygen devicesHospitalized, receiving invasive mechanical ventilationDeathChange in Horowitz index (PaO_2_/FiO_2_ ratio use to assess lung function) during hospital stay [time frame: 28 days]Change in C-reactive protein (CRP) levels, radiological findings, IL-6 level, and anti-SARS-CoV-2 antibody levels [time frame: 5 days]

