## Discussion

This phase II/III clinical trial is an adaptive, randomized controlled, multi-center, single-blinded superiority trial of SARS-CoV-2 specific polyclonal IVIG (C-IVIG) versus standard of care for patients hospitalized with severe COVID-19. Single dose of C-IVIG in combination with the standard of care was found to be both safe and efficacious in our previous clinical trial phase I/II while increasing the survival rate and reducing the risk of disease progression [13]. There were no significant changes observed when different doses of C-IVIG were compared in the phase I/II; however, it was found that C-IVIG dosage of 0.15 g/kg have significantly improved the therapeutic response in severe COVID-19 patients. These results warrant the phase II/III clinical trial study of C-IVIG, in order to evaluate its safety and efficacy in large sample size by comparing outcomes (28-mortality, hospital stay and drug-related adverse events) of C-IVIG along with SOC in intervention group and SOC only in comparator group provided during the hospital stay.

Study participant selection for this study is based on the results of our previous clinical trial where severe patients had 100% survivability and early hospital discharge than critical patients and comparator group. We evaluated that hospital stay, reliance on mechanical ventilation, and burden on hospital could be reduced if C-IVIG is administered to the severe COVID-19 patients by delaying the disease progression.

This is an adaptive clinical trial to investigate the risk-benefit analysis of C-IVIG administration for severe COVID-19 at first and second interim of the study. Major outcome variables to be assessed for interim analysis are adverse events, 28-day mortality, and change in clinical status of the patients. Fate of this clinical trial is based on whether the C-IVIG is safe and efficacious. If the treatment modality is found to be safe but not efficacious as compare to comparator group, we might select different dosage of C-IVIG for further study participants; if interim analysis indicate association of serious adverse events with administration of C-IVIG or with significant high mortality ratio in intervention group than comparator group or if incidence rate of COVID-19 is low till the study completion date, then this clinical trial would be early terminated due to aforementioned reasons.

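### Interim adverse-event monitoring is tied to giving C-IVIG, so it has no counterpart in controls, and the two termination statements differ on the role of the comparator

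*Protocol article*

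**What the plan says.** Interim analyses {21b} gives two measures in consecutive sentences. On safety: "Safety of the intervention will be monitored in terms of any immediate or serious adverse event that can be observed after the administration of the" product. Efficacy is judged by "improvement in clinical status as compared to the control group". Only the second names the control arm.

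Outcomes {12} lists as a secondary outcome "Immediate (within 24 h) or serious adverse events (throughout the hospital stay"), with a 28-day time frame. It does not say when the 24 hours begin. Intervention description {11a} gives the control arm standard hospital care only and describes no placebo infusion.

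The Discussion describes the trial as "comparing outcomes (28-mortality, hospital stay and drug-related adverse events) of C-IVIG along with SOC in intervention group and SOC only in comparator group".

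Termination is worded twice. Trial design {8}: "Outcome of the interim analysis will lead to making decision for terminating trial in case of serious adverse events". The Discussion: "if interim analysis indicate association of serious adverse events with administration of C-IVIG", or if mortality is significantly higher in the intervention group than in the comparator.

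Adverse event reporting {22} collects events from enrolment to day 28 in all participants and includes a check on whether each event is drug related. Under {17a} only participants are blinded, and under {18a} the investigators collect outcome data.

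**The concern.** Severe COVID-19 itself produces death and organ failure, as the Background notes. In such a population a count of serious events after infusion says little about the product until it is set beside the same count in concurrent controls. The {21b} sentence does not ask for that count, and its anchor, administration of the drug, does not exist for a control patient.

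The Discussion's comparison has the opposite fault. It does name both arms, but the variable can take a non-zero value in only one of them, and in that arm it rests on judgement by staff who know the allocation.

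At stake is the interim decision on adverse events. With two differently worded criteria, those reading the interim data could reach different conclusions from the same table, and neither wording calls for the all-cause comparison that {22} makes possible.

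**Working it through.** The plan gives no figure for interim safety, so there is none to reproduce. The total of 309 enters only as a headcount; how it was derived does not matter here.

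**Step 1. The passages side by side**

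- {21b}, safety: events after administration, no comparator. Undefined for controls.
- {12}, first 24 h: no stated origin. If the origin is the infusion, it is undefined for controls. Serious events during the hospital stay are definable in both arms, although a window that ends at discharge can differ in length between arms.
- Discussion, drug-related events by arm: taking the drug to be C-IVIG, the control count is 0 by construction. With *k* such events among the 31 C-IVIG patients at the first look, the difference is *k*/31 − 0/15 ≥ 0, so this comparison cannot favour C-IVIG whatever the truth.
- {8}, termination: serious adverse events, with no rate, comparator or attribution.
- Discussion, termination: association with C-IVIG, or significantly higher mortality than in the comparator. Association could mean an excess over controls or case-by-case attribution; the text does not say which.
- {22}: events from enrolment to day 28, not limited to one arm. The data for a fair comparison exist.

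**Step 2. What an uncontrolled count would contain (illustration only)**

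Inputs: 309 patients at 2:1 and survival of 75% on C-IVIG and 40% on control, from Sample size {14}, so mortality is 25% and 60%. Looks are at 15%, 30% and 60% of recruitment, from {21b}. Assumptions: death counts as a serious event (the article does not define the term), and every patient recruited by the look is followed to day 28.

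Expected deaths = patients in the arm × assumed mortality.

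- 15%: 0.15 × 309 = 46.35, about 31 C-IVIG and 15 control. Deaths 31 × 0.25 = 7.75 and 15 × 0.60 = 9.0.
- 30%: 92.7, about 62 and 31. Deaths 15.5 and 18.6.
- 60%: 185.4, about 124 and 62. Deaths 31.0 and 37.2.

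If C-IVIG had no effect at all, the first-look count would be 31 × 0.60 = 18.6. About 8 deaths among 31 treated patients is thus what the plan expects of an effective product, but only the 9 among 15 controls shows this.

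**Step 3. How far the comparative mortality criterion helps**

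Take an assumed harm of 75% against 60% mortality, two-sided 0.05, normal approximation: power = Φ[(0.15 − 1.96 × SE₀)/SE₁], with SE₀ pooled and SE₁ unpooled. At the first look SE₀ = 0.144 and SE₁ = 0.148, which gives about 19%. The second and third looks give about 32% and 56%. The criterion is valid but weak early, and it does not address non-fatal serious events.

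**The case against.** The strongest reply is that the protocol as a whole does use the control arm. All-cause 28-day mortality is the primary outcome in {12} and is named there as a measure of safety as well as efficacy. {21b} says the looks assess the primary outcome. {20a} plans a comparison of groups and a relative risk. The Discussion has a comparative mortality criterion and requires association with C-IVIG. {8} can be read as a one-line summary of that fuller rule. The phrase about drug-related events stands only in the Discussion, not in {12}, {20a} or {21b}. Numerical thresholds and event definitions may sit in the full protocol or analysis plan. Nearly all of this stands.

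It rules out several stronger readings that a reader might infer:

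- *That the trial stops on any serious event.* {8} speaks of "making decision for terminating trial in case of serious adverse events", which is a decision with no count attached. The probability of at least one C-IVIG death by the first look, 1 − 0.75^31 = 0.9999, would matter only if one death counted as a serious event and sufficed to stop. Nothing says so.
- *That disease deaths cannot be separated from drug harm.* Mortality is compared by randomised arm.
- *That safety is measured in one arm only.* {22} collects events in everyone, and the serious-event part of {12} applies to both arms.
- *That absent stopping thresholds are a defect.* They may be in documents not shown.

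The reply does not remove the anchoring of the {21b} sentence to drug administration, the missing origin of the 24-hour window for controls, the structural zero in the drug-related comparison, or the difference between the two termination statements. The relatedness check in {22} does not cure these either, because investigators who know the allocation make or influence that judgement.

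**Conclusion.** The point holds for adverse and serious adverse events and for the termination wording, not for safety assessment in general. The stated interim measure has no control counterpart, the comparison promised in the Discussion cannot favour C-IVIG, and {8} and the Discussion state different grounds for termination.

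The size is illustrative: about 8 of 31 C-IVIG and 9 of 15 control deaths by day 28 among patients recruited at the first look. This rests on the plan's assumed survival, complete 28-day follow-up, and death counting as a serious event. It shows that an uncontrolled count including deaths would mostly measure the disease. It does not show that the trial would be stopped. The zero in controls rests on reading drug-related as related to C-IVIG.

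The matter should be settled before an interim look is read, since these looks may end the trial or change the dose.

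**What to change.** In {12} and {21b}, define the safety measure as all-cause adverse and serious adverse events counted from randomisation in both arms, over the same windows (first 24 hours, and to day 28), and compare them by randomised arm. Keep investigator-judged relatedness and infusion reactions as a descriptive report for the C-IVIG arm only, and bring the Discussion's outcome list into line.

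Reconcile the termination wording in {8}, {21b} and the Discussion so that one criterion is stated. Which criterion that should be is for the sponsor and its monitors; this review does not propose one.

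The comparison also needs every randomised patient. {11b} says that a patient whose infusion is stopped for a serious adverse event will be excluded from the study. That can happen only in the C-IVIG arm and conflicts with the intention-to-treat statements in {20a} and {20c}. These passages should be reconciled so that such patients' events remain in the count.

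The cost is redrafting. {22} already collects the events from enrolment in all participants. The one added task is to record a time zero, randomisation, for control patients.

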#### Methods for additional analyses (e.g., subgroup analyses) {20b}

No subgroup analyses have been planned for this trial.

#### Methods in analysis to handle protocol non-adherence and any statistical methods to handle missing data {20c}

To handle the missing data multiple imputation will be used or complete case analysis will be used. The primary analysis will use the intention-to-treat principle.

#### Plans to give access to the full protocol, participant level-data, and statistical code {31c}

The datasets analyzed during the current study and statistical codes are available from the corresponding author on reasonable request, as is the full protocol.

### Oversight and monitoring

#### Composition of the coordinating center and trial steering committee {5d}

The study will be conducted in Dow University Hospital, Karachi, Pakistan, and Sindh infectious disease Hospital, Karachi, Pakistan.

### Composition of the data monitoring committee, its role and reporting structure {21a}

#### Adverse event reporting and harms {22}

Adverse events (AE) and serious adverse events (SE) will be observed and reported from the time of patient’s enrollment in the study till the outcome day, i.e., 28 days. AE/SE will be reported in the clinical research forms which include the time of the AE/SE medications, severity, duration of the AE, and the outcomes after AE. The relevant information of adverse events, after investigating if it is drug related or not, will be reported within 24 h to the principal investigator and to the National Drug Authorities.

#### Frequency and plans for auditing trial conduct {23}

The Clinical Research Organization (CRO) “Institute of Biological and Biochemical and Pharmaceutical Sciences (IBBPS), DUHS, Karachi” will be responsible for the auditing and monitoring of the trial. Audits may be conducted at any time during or after the study completion.

#### Plans for communicating important protocol amendments to relevant parties (e.g., trial participants, ethical committees) {25}

The modification/amendment in the protocol of this trial will be informed to the national authorities and regulators by the principal investigator. The changes will be then implemented after the approval from the authorities. Protocol amendments will also be done on trial registries such as clinicaltrial.gov and will be communicated to the journal where trial protocol has been published. After any protocol amendment, the informed consent form and any other written information provided to the subjects will be updated as necessary.

#### Dissemination plans {31a}

The results will be reported to the national authorities such as National Bioethics Committee (NBC) and Drug Regulatory Authority of Pakistan (DRAP) and will be published in the reputed scientific journals, to communicate trial results to participants, healthcare professionals, the public, and other relevant groups.

## Discussion

This phase II/III clinical trial is an adaptive, randomized controlled, multi-center, single-blinded superiority trial of SARS-CoV-2 specific polyclonal IVIG (C-IVIG) versus standard of care for patients hospitalized with severe COVID-19. Single dose of C-IVIG in combination with the standard of care was found to be both safe and efficacious in our previous clinical trial phase I/II while increasing the survival rate and reducing the risk of disease progression [13]. There were no significant changes observed when different doses of C-IVIG were compared in the phase I/II; however, it was found that C-IVIG dosage of 0.15 g/kg have significantly improved the therapeutic response in severe COVID-19 patients. These results warrant the phase II/III clinical trial study of C-IVIG, in order to evaluate its safety and efficacy in large sample size by comparing outcomes (28-mortality, hospital stay and drug-related adverse events) of C-IVIG along with SOC in intervention group and SOC only in comparator group provided during the hospital stay.

Study participant selection for this study is based on the results of our previous clinical trial where severe patients had 100% survivability and early hospital discharge than critical patients and comparator group. We evaluated that hospital stay, reliance on mechanical ventilation, and burden on hospital could be reduced if C-IVIG is administered to the severe COVID-19 patients by delaying the disease progression.

This is an adaptive clinical trial to investigate the risk-benefit analysis of C-IVIG administration for severe COVID-19 at first and second interim of the study. Major outcome variables to be assessed for interim analysis are adverse events, 28-day mortality, and change in clinical status of the patients. Fate of this clinical trial is based on whether the C-IVIG is safe and efficacious. If the treatment modality is found to be safe but not efficacious as compare to comparator group, we might select different dosage of C-IVIG for further study participants; if interim analysis indicate association of serious adverse events with administration of C-IVIG or with significant high mortality ratio in intervention group than comparator group or if incidence rate of COVID-19 is low till the study completion date, then this clinical trial would be early terminated due to aforementioned reasons.

## Trial status

Study start date: August 1, 2021

Protocol version: 3

Anticipated completion date: December 2, 2022

## Data Availability

Final trial dataset will be made available to others. Data will be available from publication till 1 year. Any request for the data could be sent to [contact]. There are no contractual agreements that can limit access of investigators to the final trial dataset.

## Abbreviations

ARDS: Acute respiratory distress syndrome
C-IVIG: Hyperimmune anti-COVID-19 intravenous immunoglobulin
CP: Convalescent plasma
CRF: Clinical research form
CRO: Clinical Research Organization
CTU: Clinical Trial Unit
DRAP: Drug Regulatory Authority Pakistan
SARS-CoV-2: Severe acute respiratory syndrome coronavirus 2
SE: Severe adverse events
SIDH: Sindh Infectious Disease Hospital
